### Sample size and power calculation

Table 3 shows the power to detect correlations of at least a given magnitude at *p* < 0.01 for recruited sample sizes of 500, 750, or 1000 paired observations (mother-child pairs, calculated with adjustment assuming 10% attrition). An alpha level of 0.01 was selected because four primary analyses are planned to correlate maternal glycemia, serum lipids, inflammatory markers, and kidney function with each primary outcome (offspring birthweight and body size up to 24 months of age). A target sample size of 750 maternal-offspring pairs is proposed, as this will provide ~ 90% power to detect a correlation coefficient of 0.15, which we take to be biologically meaningful (Table 3). Genome-wide genetic and epigenetic studies (and other studies in which large numbers of exposure variables are measured simultaneously) will require more stringent control of type I error to account for multiple testing; typically, this requires *P* < 10^− 7^ [18]. With such stringency, effect sizes will need to be somewhat larger than in standard analyses for reliable detection; with the target sample size of 750, the minimum detectable correlation at *P* < 10^− 7^ with 80% power is 0.23. We will use the false discovery rate procedure to control the type I error rate [19].

**Table 3 Tab3:** Sample size and power calculations

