### Study outcomes and data collection

The primary outcomes are birth weight, and weight, length, and age/sex adjusted BMI percentile and z-scores at 6–12 weeks, 4, 6, 12, 18, and 24-months. Secondary outcomes include BMI percentile and z-scores from 2 to 18 years of age, stool microbiome (microbial taxonomies, microbial pathways), hepatic steatosis and fibrosis, neurocognitive development, assessments of environmental and psychosocial status and biochemical measures for glycemia, lipids, renal, and liver function.

Data are collected either by in-person assessment, by review of medical records, by phone or other virtual media or a combination following the schedule of activities in Table 1. Data collected on mothers include demographics, anthropometric measures, socioeconomic and family environment history, medical history, obstetric history, laboratory evaluations, and biospecimens (blood, urine, stool, cord blood, placental tissue, and breast milk). Data collected on offspring include demographics, birth history, socioeconomic history such as living situation, childcare arrangements, parental education and employment, food insecurity, cultural practices during pregnancy, medical history, assessments of lifestyle habits such as eating and activity patterns, sleep, perceived stress, laboratory evaluations, and biospecimens (blood, urine, and stool). DNA and RNA data are collected on both mothers and offspring. The data collected in ETCHED are summarized in Table 2. Some of the information related to medical history of mothers and/or offspring is obtained by direct interview, by review of medical records, or both.

**Table 2 Tab2:** Data collected in ETCHED

Participant	Type	Collected data
Mother	Demographic, socioeconomic and family environment history	• Age, race/ethnicity, marital status, approximate age of child’s father, father’s race ethnicity, father’s diabetes status • Highest level of education of parents, family size, family employment history, family income, family ownership, family hardships, household characteristics • Childcare arrangements
	Medical record review	• Clinical information, laboratory and radiological information • This includes demographic, anthropometric, clinical history, results of imaging studies, and biochemical data (will focus on periodic measures related to glycemia).
	Medical history	• Underlying health conditions, new illnesses or hospitalizations between visits, maternal history of COVID-19 infection

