### **Analysis of the** primary outcomes

As described above, to examine associations among maternal risk measures, and offspring weight and body size, scatterplots and grouped box plots will be constructed to examine assumptions of linearity, symmetry, and homoscedasticity. To model changes in childhood BMI over time, we will use mixed effects models to fit a piecewise growth curve model which predicts childhood BMI as a function of time.

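### The 0.01 significance level allows for four primary tests, but the plan crosses four exposures with 19 to 25 primary outcomes

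*Protocol article*

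**What the plan says.** Under Sample size and power calculation, the protocol article explains its threshold: "An alpha level of 0.01 was selected because four primary analyses are planned". The sentence goes on to say that these analyses will "correlate maternal glycemia, serum lipids, inflammatory markers, and kidney function with each primary outcome", and glosses the outcomes as birth weight and body size up to 24 months. Table 3 gives power of 0.92 for a correlation of 0.15 with 750 pairs recruited and 675 analysed.

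Study outcomes and data collection sets out the outcomes in full: "The primary outcomes are birth weight, and weight, length, and age/sex adjusted BMI percentile and z-scores", the last group measured at six ages, "z-scores at 6–12 weeks, 4, 6, 12, 18, and 24-months". No lead outcome or lead age is named.

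Two other statements bear on multiplicity. After the genome-wide text, the sample size section ends: "We will use the false discovery rate procedure to control the type I error rate". Under Analysis of the primary outcomes, mixed effects models are to "fit a piecewise growth curve model which predicts childhood BMI as a function of time". Neither statement is linked to the 0.01 level. Statistical analysis says that the major analyses are correlation coefficients between continuous variables.

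**The concern.** The stated reason for 0.01 counts exposures and leaves out outcomes. If each exposure is correlated with each listed outcome at p<0.01, the primary set contains many times the four tests allowed for, and nothing in the text says which of them carries the conclusion. An isolated primary association at p<0.01 would then be weaker evidence than the rationale suggests. The power statement is affected as well, because it rests on a threshold that does not match the number of tests described.

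**Working it through.** **Inputs.** Level 0.01 (taken as two-sided; the article does not say), four exposures, 675 analysed pairs and r = 0.15, all from Sample size and power calculation and Table 3. Outcomes and ages are from Study outcomes and data collection. Correlations among outcomes and among exposures are not given and are assumed below.

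**1. Reproducing the plan's power.** Fisher z: power = Φ(atanh(r)·√(n−3) − z₁₋α/₂).

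- atanh(0.15)·√672 = 0.1511 × 25.92 = 3.918.
- At α = 0.01: 3.918 − 2.576 = 1.342, power 0.910. Table 3 prints 0.92.
- At α = 0.0125 (= 0.05/4): 3.918 − 2.498 = 1.420, power 0.922.

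All nine cells of Table 3 match α = 0.0125. Four of them miss by more than two points at the labelled 0.01 (0.35 against 0.325, 0.76 against 0.732, 0.54 against 0.510, 0.69 against 0.666). The table therefore appears to have been computed for exactly four tests. This is an inference from the figures; the article does not say so.

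**2. Counting the tests.**

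- Weight, length, BMI percentile and BMI z-score at six ages, plus birth weight: 1 + 4×6 = 25 outcomes; ×4 exposures = 100 tests.
- Percentile and z-score counted as one measure: 1 + 3×6 = 19 outcomes; ×4 = 76 tests.
- Narrowest reading, birth weight and a single body-size outcome: 2×4 = 8 tests.

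**3. Chance of at least one p<0.01 when no exposure has an effect.** For k independent tests it is 1 − 0.99^k.

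| Tests | Independent |
|---|---|
| 4 | 3.9% |
| 8 | 7.7% |
| 76 | 53.4% |
| 100 | 63.4% |

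Growth measures on one child are correlated, which lowers these figures. Simulation with four independent exposures and 25 outcomes, all pairs of outcomes equally correlated, gives:

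| Assumed correlation | At least one p<0.01 |
|---|---|
| 0.5 | 45% |
| 0.7 | 31% |
| 0.8 | 24% |
| 0.9 | 16% |
| 0.95 | 11% |

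With separate correlations between visits (0.9 down to 0.5) and between measures, the range is about 25–44%. The highest values, just under 50%, arise when a correlation of 0.5 between adjacent visits decays with distance. Taken together, correlations of 0.5 to 0.95 give about 11–49%. For the eight-test reading, correlation 0.95 gives about 5.4%.

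**4. If the false discovery rate sentence covers these tests.** Benjamini–Hochberg at 5% over the 100 tests, with no true effects, gives at least one rejection in 2.6% of simulations at correlation 0.8, and about 2–5% across the structures tried.

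**5. Power for other families (r = 0.15, n = 675, Bonferroni).**

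| Tests | Level per test | Power |
|---|---|---|
| 6 | 0.0083 | 0.90 |
| 8 | 0.00625 | 0.88 |
| 76 | 0.00066 | 0.70 |
| 100 | 0.0005 | 0.67 |

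**The case against.** The strongest reply is that 100 tests is only one reading. The sample size sentence itself summarises the outcomes as birth weight and body size, and a mixed model for BMI over time is planned under the primary outcomes. Pooled in that way, there are about eight tests. This stands as a limit on the size of the problem, but the rate is still 5.4–7.7%, and the model is not tied to the 0.01 level.

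Second, the family might be meant per outcome, in which case four tests do hold 3.9% within each. The article does not say this, and every such family would still be labelled primary.

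Third, the false discovery rate sentence may govern the primary tests. If so, the excess under no effects disappears (step 4). But the rule would then replace the fixed p<0.01 on which the power statement is based. As the sentence follows the genome-wide text, its scope cannot be settled from the article.

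Fourth, an observational study that estimates correlations need not control family-wise error strictly, and no family-wise target is stated. That is fair. Still, this study chose its level expressly because of the number of analyses, so the count should match the plan.

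A reader might also infer that the growth model leaves out the maternal exposure, because it is described as a function of time. The article does not support that: the preceding sentence concerns associations with maternal risk measures, and model terms are commonly left to the full protocol or SAP.

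**Conclusion.** The four-test rationale does not cover the analyses described. Holding p<0.01 for each test, the chance of at least one false-positive primary result is above the roughly 4% implied: 53–63% under independence, about 11–49% for outcome correlations of 0.5 to 0.95, and about 5–8% on the narrowest reading. The direction was the same in every four-exposure scenario tried. The size depends on correlations that the article does not give, so no single percentage should be quoted as the study's error rate.

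Two stronger conclusions are tempting. A reader might infer that a chance finding is to be expected, since 100 × 0.01 = 1 false positive on average. But false positives among correlated outcomes cluster, and under the correlations assumed here the chance of none is still about 51–89%. A reader might also infer that the stated power of about 90% is lost. That follows only if all 76 to 100 tests are given a Bonferroni correction (0.70 to 0.67), which the article does not propose; a small primary family keeps power near the stated figure.

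What needs correction is therefore the definition of the primary family and the rule that governs it.

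**What to change.** - **Reconcile the exposures first.** Study objectives names three (pre-pregnancy BMI, gestational weight gain, glycemia); the sample size section names four (glycemia, lipids, inflammatory markers, kidney function). Name one variable for each exposure kept as primary, since Table 2 lists several lipids and several inflammatory markers.
- **Pre-specify two outcomes per primary exposure:** birth weight, and a single test of BMI z-score over 0–24 months from the planned mixed model, with the maternal exposure included.
- **Apply Holm at 0.05** across that family: six tests with three exposures, eight with four.
- **Treat the per-visit correlations and BMI percentile as supporting** results.
- **State that the false discovery rate procedure applies to the omics analyses.**
- **Restate power and Table 3** at the level actually used. For a single correlation of 0.15 with 675 pairs, Bonferroni gives 0.90 for six tests and 0.88 for eight; Holm is never less powerful. The mixed-model test needs its own calculation, since these figures are for a simple correlation.

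The cost is wording in the protocol and SAP. Per-visit correlations lose confirmatory status, and the stated power may fall slightly. No change to recruitment, visits or data collection is needed.

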	**Pearson correlation coefficient**		
	0.10	0.15	0.20
**Sample size**		**Power**	
500* (450)	0.35	0.76	0.96
750* (675)	0.54	0.92	> 0.99
1000* (900)	0.69	0.98	> 0.99

*Adjusted sample size accounting for 10% attrition

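### Table 3 is labelled as power at p < 0.01, but its values do not reproduce at two-sided 0.01 and all nine match at 0.0125 (0.05/4); a minor mismatch that leaves the sample size unaffected

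*Protocol article*

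**What the plan says.** The section on sample size and power in the Protocol article introduces the table with "Table 3 shows the power to detect correlations of at least a given magnitude" and sets the level at p < 0.01. The columns are headed "Pearson correlation coefficient", with values 0.10, 0.15 and 0.20. The rows are recruited sizes of 500, 750 and 1000, described as "mother-child pairs, calculated with adjustment assuming 10% attrition", so the retained sizes in the table are 450, 675 and 900.

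The reason given for the level is the number of analyses: "An alpha level of 0.01 was selected because four primary analyses are planned". The same sentence names them: "four primary analyses are planned to correlate maternal glycemia, serum lipids, inflammatory markers, and kidney function with each primary outcome".

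On the design itself the article says "A target sample size of 750 maternal-offspring pairs is proposed", giving about 90% power "to detect a correlation coefficient of 0.15, which we take to be biologically meaningful". The same section also gives a minimum detectable correlation of 0.23 at P < 10⁻⁷ with 80% power for the genome-wide work. It does not say whether the tests are one- or two-sided.

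**The concern.** A power table belongs to one significance level. Here the text names 0.01, while the printed figures fit a slightly looser level. The reason offered for 0.01, four analyses, would give 0.05/4 = 0.0125 under a Bonferroni split of 0.05. The document therefore points to two thresholds.

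Two things follow. A reader who takes 0.01 at face value sees somewhat more power than that threshold delivers. And a primary correlation with a p-value between 0.01 and 0.0125 would be judged differently depending on which level is meant.

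**Working it through.** **Inputs.** From the article: retained n = 450, 675, 900; r = 0.10, 0.15, 0.20; alpha 0.01; test of a Pearson correlation against zero. Assumed, because not stated: two-sided testing.

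**Formula.** Power = Φ(atanh(r)·√(n − 3) − z) + Φ(−atanh(r)·√(n − 3) − z), where z is the 1 − α/2 normal quantile. The second term is negligible here. z = 2.5758 at α = 0.01 and 2.4977 at α = 0.0125.

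**Check of method and n on another figure in the same section.** The minimum detectable correlation at P < 10⁻⁷ with 80% power is tanh((5.3267 + 0.8416)/√(n − 3)). For n = 675, √672 = 25.923 and the result is 0.234, which agrees with the stated 0.23. For n = 750 it is 0.222, which does not. So two-sided Fisher z with the retained n is consistent with the article's other calculation.

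**The design cell, n = 675 and r = 0.15.** atanh(0.15) = 0.15114, and 0.15114 × 25.923 = 3.918.
- α = 0.01: Φ(3.918 − 2.576) = Φ(1.342) = 0.910
- α = 0.0125: Φ(3.918 − 2.498) = Φ(1.420) = 0.922
- Printed: 0.92

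**The cell with the largest gap, n = 675 and r = 0.10.** atanh(0.10) = 0.10034, and 0.10034 × 25.923 = 2.601.
- α = 0.01: Φ(0.025) = 0.510
- α = 0.0125: Φ(0.103) = 0.541
- Printed: 0.54

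**All nine cells.**

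| n | r | Printed | α = 0.01 | α = 0.0125 |
|---|---|---|---|---|
| 450 | 0.10 | 0.35 | 0.325 | 0.353 |
| 450 | 0.15 | 0.76 | 0.732 | 0.757 |
| 450 | 0.20 | 0.96 | 0.956 | 0.963 |
| 675 | 0.10 | 0.54 | 0.510 | 0.541 |
| 675 | 0.15 | 0.92 | 0.910 | 0.922 |
| 675 | 0.20 | >0.99 | 0.996 | 0.997 |
| 900 | 0.10 | 0.69 | 0.666 | 0.694 |
| 900 | 0.15 | 0.98 | 0.974 | 0.979 |
| 900 | 0.20 | >0.99 | >0.999 | >0.999 |

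To four decimals the first cell at 0.01 is 0.3247, so it rounds to 0.32. At 0.01, six of the seven cells printed as exact values fail to match at two decimals, all in the same direction. At 0.0125 every cell matches.

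**Other explanations tried.**
- One-sided 0.01 overshoots by up to 7 points (for example 0.61 where 0.54 is printed).
- Ignoring attrition at 0.01 gives 0.37/0.79/0.97 in the first row, which is also wrong.
- Other two-sided formulas at 0.01 do not close the gap. A noncentral chi-square version still leaves 2.6 points.
- Scanning alpha with Fisher z in steps of 0.0001, only about 0.0123 to 0.0125 reproduces all nine cells. A noncentral t with a fixed predictor needs about 0.0119 to 0.0123. Neither range reaches 0.01.

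**The case against.** The strongest reply is that this is only a label. On this view 0.05/4 = 0.0125 was shortened to 0.01 in the article, the table is correct, and the four-analysis rationale shows what was meant. That is plausible, and the document does not exclude it. It limits what can be said: the text and the table disagree, but the document does not settle which of them is the slip.

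The reply is also right about consequence. The design rests on r = 0.15 with 750 recruited, and there the power at 0.01 is 0.910. The largest gap is at r = 0.10, which is not the correlation the study was sized on, and the 500 and 1000 rows are alternatives that were not chosen.

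A reader might go further and infer that the study is underpowered at its stated threshold, or that the plan is left without a valid power statement. The documents support neither. The statement of about 90% power holds at 0.01, and the separate figure of 0.23 at P < 10⁻⁷ reproduces with 675 pairs.

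What remains after the reply is the mismatch itself. Nothing else in the article reconciles the stated level with the table, and 0.0125 is not printed anywhere.

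**Conclusion.** The point holds as a minor inconsistency. Table 3 is not power at a two-sided 0.01; it fits 0.0125. If 0.01 is the level to be used, the exact-valued cells overstate power by between 0.4 points (0.96 against 0.956) and 3 points (0.54 against 0.510), and by about 1 point at the design cell. If 0.0125 is the level, the table stands and the stated alpha is wrong. The target of 750 is sound either way.

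This rests on two-sided testing and on the retained sizes printed in the table. That 0.0125 was the level used, and that it came from splitting 0.05 over four analyses, are inferences from the numerical match and the stated rationale.

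**What to change.** Choose one alpha and use it in the text, in Table 3 and in the analysis. Say that it is two-sided, if that is so. Either of these will do:

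- State the threshold as 0.0125 = 0.05/4 and leave Table 3 as it is.
- Keep 0.01 and replace the power values (r = 0.10/0.15/0.20) with 0.32/0.73/0.96 for 450 retained pairs, 0.51/0.91/>0.99 for 675 and 0.67/0.97/>0.99 for 900.

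The cost is one sentence or one small table. The second option makes the stated power slightly less favourable. Neither changes the sample size or the claim of about 90% power at r = 0.15.

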The primary aim of the Early Tracking of Childhood Health Determinants (ETCHED) study is to examine the associations of maternal risk factors, including pre-pregnancy body mass index, gestational weight gain, and glycemia during pregnancy with offspring birth weight, length, and age/sex adjusted body mass index (BMI) percentile and z-score from birth until 2 years of age; a secondary objective includes studying these associations with BMI percentile and z-score from 2 to 18 years. Other secondary objectives study the role of maternal clinical, genetic, biochemical, lifestyle, and psychosocial factors during pregnancy in mediating the associations between maternal risk factors and birth weight of the offspring, and weight, adiposity, metabolic profile, and neurodevelopment; this during infancy, childhood, and adolescence. The ETCHED study will only enroll participants of Hispanic ethnicity and/or American Indian.

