### Study objectives

The primary objective is to investigate the associations of maternal risk factors including pre-pregnancy body mass index (BMI), gestational weight gain, and glycemia with offspring’s birth weight, and weight and adiposity during infancy (0–24 months of age).

Secondary objectives of the ETCHED study include:

Studying the associations of maternal risk factors (pre-pregnancy BMI, gestational weight gain, and glycemia) with weight, adiposity, and physical growth patterns during childhood and adolescence (2–18 years of age).Studying the role of maternal clinical, genetic, biochemical, lifestyle, and psychosocial factors during pregnancy in mediating the associations between maternal risk factors and birth weight of the offspring, and weight, adiposity metabolic profile, and neurodevelopment during infancy, childhood, and adolescence.Examining the role of family, socioeconomic, and environmental factors influencing child growth patterns, body composition and neurodevelopment in infancy and childhood.To assess the frequency of hepatic steatosis in children and its association with BMI and biochemical alterations.Examining the relationship between maternal risk factors, early childhood exposures, and changes in gut microbiome during infancy, childhood, and adolescence.Studying the associations of maternal risk factors, including pre-pregnancy BMI, gestational weight gain, and glycemia and placental function, methylome, transcriptome, proteome and metabolome with weight, adiposity, and physical growth patters during childhood and adolescence (2–18 years of age).

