	Obstetric history	• Pre-pregnancy weight, delivery date(s), APGAR score, sex, weight, length, gestational age, prenatal and perinatal history, pregnancy outcomes
	Laboratory evaluations	• From blood: blood complete blood count, HbA1c, fasting glucose and insulin, adiponectin, TNF, IL-6, folate, CRP, and cytokines, biological markers for obesity and metabolic dysfunction, liver function tests, serum cholesterol, triglycerides, HDL and LDL cholesterol, apolipoproteins • Oral glucose tolerance test in the research clinic postpartum
	Biospecimens	• Blood for DNA, RNA • Stool for microbiome analysis • Breastmilk
	Mother’s procedures	• Physical exam [height, weight, waist circumference (non-pregnant) and blood pressure measurement] • Questionnaires: Unmet Social Support, Modifiable Activity Questionnaire, Pittsburg Sleep Quality Index, Adverse Childhood Experience, BLOCK-2000, Food Insecurity Questionnaire, Eating Behaviors (EARLY), Cohen’s perceived Stress Scale, Short Acculturation Scale for Hispanics (SASH) if appropriate, and cultural consideration survey
Infant	Birth history (by medical record review)	• Neonatal history such as mode of delivery, birth, weight, height, and head circumference, gestational age, APGARS, neonatal/perinatal complications, congenital anomalies
	Medical history	• Mother will be asked about: vaccination history, history of illness, including COVID diagnosis, antibiotics use, hospitalizations, ED visits, any new diagnosis.
	Medical record review	• Clinical, laboratory, and radiological information
	Laboratory evaluation	• Blood will be drawn for CBC, HbA1c, insulin, and lipids
	Biospecimens	• Cord blood for Hba1c, insulin, biomarkers such as c-peptide, leptin, adiponectin, TNF-alpha; other novel metabolomics, genetic and epigenetic tests. SARS-COVID 19 antibody • Placenta tissue for subsequent analysis of placenta function, methylome, transcriptome, proteome, metabolome, histopathology and histochemistry • Blood draw for DNA and RNA • Meconium and stool for microbiome analysis

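### The four primary analyses that justify alpha leave out two of the three maternal exposures named in the primary objective

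*Protocol article*

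**What the plan says.** The Background gives the primary aim as to "examine the associations of maternal risk factors, including pre-pregnancy body mass index, gestational weight gain, and glycemia during pregnancy" with offspring size at birth and up to 2 years. Study objectives repeats the list: "The primary objective is to investigate the associations of maternal risk factors including pre-pregnancy body mass index (BMI), gestational weight gain, and glycemia", again in relation to birth weight and to infant weight and adiposity. The exposures are the same three in both places.

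The section on sample size and power uses a different list. It sets alpha at 0.01 because "four primary analyses are planned to correlate maternal glycemia, serum lipids, inflammatory markers, and kidney function with each primary outcome". Pre-pregnancy BMI and gestational weight gain are absent. In Study objectives, maternal biochemical factors appear under a secondary objective, as possible mediators.

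Statistical analysis describes the major analyses as correlations between continuous variables, with maternal glycemia as the example. It mentions maternal BMI and weight gain only when it introduces the mediation models. Analysis of the primary outcomes refers to maternal risk measures in general and names none.

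**The concern.** The alpha level is justified by a count of primary analyses, so the items counted are the declared primary family. If that family is not the one in the primary objective, the article gives two answers to which exposure associations are primary.

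Followed literally, the sample-size section gives primary status to lipids, inflammatory markers and kidney function and withholds it from pre-pregnancy BMI and gestational weight gain, which head the list in the stated aim. A reader of the eventual results could not tell from this article whether a BMI or weight-gain association was one of the tests that alpha was set to protect. If those two are primary as well, the count of four is wrong and so is the reason given for 0.01.

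**Working it through.** **1. Compare the lists.**

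| Maternal exposure | Primary aim and objective | Four primary analyses |
|---|---|---|
| Glycemia | named | named |
| Pre-pregnancy BMI | named | absent |
| Gestational weight gain | named | absent |
| Serum lipids | not named | named |
| Inflammatory markers | not named | named |
| Kidney function | not named | named |

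One exposure is shared. The union has 3 + 4 − 1 = 6 exposures.

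**2. Reproduce the plan's power.** Inputs from the sample-size section and Table 3: r = 0.15, 750 pairs recruited, 10% attrition, so 750 × 0.9 = 675 analysed. Sidedness is not stated; two-sided is assumed. Fisher z approximation:

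power = Φ(atanh(r) × √(n − 3) − z(1 − α/2))

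atanh(0.15) = 0.1511 and √672 = 25.92, so the first term is 3.918. At α = 0.01, z = 2.576 and power = Φ(1.342) = 0.910. This agrees with the text's figure of about 90%; Table 3 prints 0.92.

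**3. Check the rest of Table 3.** Each cell shows r = 0.10 / 0.15 / 0.20.

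| Analysed n | Printed | α = 0.01 | α = 0.0125 |
|---|---|---|---|
| 450 | 0.35 / 0.76 / 0.96 | 0.325 / 0.732 / 0.956 | 0.353 / 0.757 / 0.963 |
| 675 | 0.54 / 0.92 / >0.99 | 0.510 / 0.910 / 0.996 | 0.541 / 0.922 / 0.997 |
| 900 | 0.69 / 0.98 / >0.99 | 0.666 / 0.9745 / >0.99 | 0.694 / 0.979 / >0.99 |

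All nine cells match at 0.0125 = 0.05/4. At 0.01 the six cells for r = 0.10 and r = 0.15 differ from print at two decimals. One-sided 0.01 does not fit (0.419 / 0.608 / 0.751 down the r = 0.10 column), nor does a noncentral t calculation at two-sided 0.01 (0.326 / 0.512 / 0.668 down the same column). The count of four therefore seems to have entered the power calculation itself.

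**4. Effect of changing the list.** Power for r = 0.15, n = 675, two-sided, with 0.05 divided over exposures only:

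| Primary family | α per test | Power |
|---|---|---|
| Objective's three | 0.05/3 = 0.0167 | 0.936 |
| Sample-size section's four | 0.05/4 = 0.0125 | 0.922 |
| Any list, α kept as stated | 0.01 | 0.910 |
| All six | 0.05/6 = 0.0083 | 0.900 |

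With every test at 0.01, the upper bound on the error rate per outcome is 3 × 0.01 = 0.03, 4 × 0.01 = 0.04 or 6 × 0.01 = 0.06.

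**The case against.** The strongest reply is that the objective's list is open. Both the aim and the objective say *including* before the three exposures, so lipids, inflammatory markers and kidney function may count as maternal risk factors. That stands, and for this reason it would be wrong to say that three of the four analyses fall outside the objective; they are only not named in it. But an open list can add exposures. It cannot explain why two that are named, in both places, are missing from the four.

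A second reply is that the general wording in Statistical analysis and in Analysis of the primary outcomes covers BMI and weight gain. This also stands in part. A reader might infer that these exposures will not be analysed at all, and the documents do not support that. Neither section designates them as primary tests, however, and if they are primary the family has six members, not four.

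A third reply is that an analysis plan not shown may settle the matter. That is a fair answer on which analyte represents lipids or inflammation, or which visit supplies the glycemia value, and no point is made of those here. It does not answer two conflicting statements in the article itself.

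A reader might also infer from Table 2, which names no maternal kidney measure, that kidney function is not collected in mothers. The Abstract lists renal function among the standard maternal laboratory tests, and Table 1 schedules maternal blood and urine labs in all three gestational windows, so that inference fails.

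**Conclusion.** The contradiction is real and concerns the definition of the primary family. Two of the three exposures named in the primary aim and objective are not among the four analyses that justify alpha, and three exposures not named there are.

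The stronger inference, that the study is wrongly sized, is not supported. Power for r = 0.15 at 675 pairs stays at about 0.90 to 0.94 whether the family has three, four or six exposures. This assumes two-sided tests, the article's 10% attrition and a Bonferroni division over exposures only; multiplicity across outcomes and ages is not counted. What is affected is interpretation: which associations may be reported as primary, and at what alpha.

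The mismatch between the stated 0.01 and the 0.0125 that reproduces Table 3 is a smaller error. It should be corrected at the same time.

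**What to change.** Make the primary exposure list identical in the Background, Study objectives and the sample-size section. The preferred route is to put pre-pregnancy BMI, gestational weight gain and glycemia in the sample-size section and make lipids, inflammatory markers and kidney function secondary, which agrees with the mediator role that the secondary objective gives to biochemical factors. The alternative is to declare all six primary in all three places.

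Then restate alpha with its reason for the chosen family, and recompute Table 3 at that alpha. A three-exposure family does not by itself justify loosening alpha to 0.0167, because the analyses are to be run against each primary outcome; keeping 0.01 still gives power of 0.910.

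The cost is a wording change and a re-run of one table, with no new data and no change to the target of 750 pairs. Under the first route the lipid, inflammatory and renal correlations lose primary status. Under the second, an even split of 0.05 gives alpha of 0.0083 and power of about 0.90. The change should be made before the primary analyses are run.
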